## Abstract

**Background:**

Chest pain is the second most common reason patients visit emergency departments (EDs) and often results in very low-risk patients being admitted for prolonged observation and advanced cardiac testing. Shared decision-making, including educating patients regarding their 45-day risk for acute coronary syndrome (ACS) and management options, might safely decrease healthcare utilization.

**Methods/Design:**

This is a protocol for a multicenter practical patient-level randomized trial to compare an intervention group receiving a decision aid, Chest Pain Choice (CPC), to a control group receiving usual care. Adults presenting to five geographically and ethnically diverse EDs who are being considered for admission for observation and advanced cardiac testing will be eligible for enrollment. We will measure the effect of CPC on (1) patient knowledge regarding their 45-day risk for ACS and the available management options (primary outcome); (2) patient engagement in the decision-making process; (3) the degree of conflict patients experience related to feeling uninformed (decisional conflict); (4) patient and clinician satisfaction with the decision made; (5) the rate of major adverse cardiac events at 30 days; (6) the proportion of patients admitted for advanced cardiac testing; and (7) healthcare utilization. To assess these outcomes, we will administer patient and clinician surveys immediately after each clinical encounter, obtain video recordings of the patient-clinician discussion, administer a patient healthcare utilization diary, analyze hospital billing records, review the electronic medical record, and conduct telephone follow-up.

**Discussion:**

This multicenter trial will robustly assess the effectiveness of a decision aid on patient-centered outcomes, safety, and healthcare utilization in low-risk chest pain patients from a variety of geographically and ethnically diverse EDs.

**Trial registration:**

NCT01969240.

## Background

Chest pain is the second most common reason patients visit emergency departments (EDs) across the United States, accounting for over 8 million visits and 25% of hospital admissions annually
[1,2]. Information from the history and physical examination, electrocardiogram, and initial cardiac troponin alone lack sufficient sensitivity to reliably eliminate patients without acute coronary syndrome (ACS) who are safe for ED discharge. As missed ACS may lead to an acute myocardial infarction (AMI) and/or potentially preventable death or disability, clinicians have a low threshold to hospitalize patients with chest pain. This results in increased psychological morbidity for patients - including anxiety and depression - and hospital overcrowding, increased false positive test results, unnecessary downstream procedures, and between 3 and 10 billion dollars spent annually for patients found not to have cardiac disease
[3,4].

Several contemporary prediction rules for ED patients with possible ACS have been developed and validated
[5-9]. To date, however, none have been widely adopted by clinicians and consistently translated into practice. A recent trial suggests that it may be feasible to discharge low-risk patients with possible cardiac chest pain from the ED without cardiac stress testing or a computed tomography (CT) coronary angiography
[10]. However, ED patients being evaluated for possible ACS are rarely aware of their risk for an adverse cardiac event,
[11] and in one recent trial lower patient satisfaction was observed in the intervention arm in which clinicians used evidence-based decision support without explicit risk communication and patient engagement
[12].

In the context of emergency medicine, clinicians frequently practice under conditions of high patient volume and acuity and are often required to make decisions expeditiously to ensure the safety of patients waiting to be seen. The approach clinicians take to medical decision-making may vary based on any number of factors, such as the degree of patient acuity, the cognitive workload of the clinician at a particular moment in time, and their perception of a patient’s desire to engage in decisions regarding their care, among others. Moreover, the approach adopted at the onset of a medical encounter may change as the interaction evolves
[13]. One way to think of this is as a fluid process, in which an experienced clinician seamlessly transitions from one decision-making model to the next, depending on the approach that seems most appropriate given the clinical context and the individual patient.

In prior work we developed a decision aid, Chest Pain Choice (CPC),
[14] and tested the hypothesis that use of the decision aid during a clinical encounter would facilitate a shared approach to medical decision-making, improve patient-centered decision-based outcomes (patient knowledge, engagement in the decision-making process and satisfaction), and safely decrease resource utilization. The decision aid described to patients the rationale for their chest pain evaluation and the potential utility of urgent cardiac stress testing. It also included a precise estimate of the 45-day risk for ACS derived from a robustly validated prediction model
[5,15,16] and communicated that risk using prose phrases, numbers, and a pictograph to account for the patient’s preferred mode of understanding numerical information
[14]. In a single-center randomized pilot trial (n = 204) we observed greater knowledge regarding management options and the short-term risk for ACS, greater engagement in the decision-making process, and a 19% lower rate of observation unit admission for cardiac stress testing in patients randomized to this shared decision-making intervention compared to usual care, and there were no major adverse cardiac events within 30 days in either arm
[11].

In this paper we describe the rationale and methods employed to test the effectiveness of the CPC decision aid in a multicenter trial in five geographically and ethnically diverse hospital EDs in the United States. We hypothesize that use of the decision aid will significantly increase patient knowledge, engagement and satisfaction, and decrease the rate of testing that may have marginal benefit in the low-risk population with no increase in adverse events.

## Methods/Design

This practical, multicenter randomized trial compares an intervention group receiving a structured risk assessment and corresponding decision aid (CPC), to a control group receiving usual care
[17]. Institutional Review Board approval has been obtained at each participating institution. The trial is registered at clinicaltrials.gov (NCT01969240).

### Setting

Patients and physicians will be recruited from five EDs: the University of Pennsylvania in Pennsylvania, United States (east coast with an urban patient population); the Mayo Clinic in Rochester, Minnesota, United States (midwest with a rural patient population); the Mayo Clinic in Jacksonville, Florida, United States (southeast with an urban patient population); the University of California, Davis in California, United States (west coast with an urban patient population); and Indiana University Health Methodist Hospital in Indianapolis, Indiana, United States (midwest with an urban patient population). We selected these five settings to assess the effectiveness of the decision aid in geographically diverse clinical practice contexts and ethnically diverse patient populations. The trial will be conducted in the flow of routine patient care.

### Participants

#### Participant recruitment

A study coordinator will identify potentially eligible patients based on the chief complaint and, in collaboration with the treating clinician, confirm patient eligibility for the trial (Figure 
1). The study coordinator will then obtain written informed consent from the patient. Consent will be obtained from participating clinicians before or at the time of patient consent. Patients will be consecutively enrolled at each of the participating centers six to seven days per week whenever a study coordinator is available for enrollment.

**Figure 1 F1:**
[figure not shown]
**Flow diagram showing the integration of study procedures in the flow of patient care.** *Candidacy for ED observation unit admission will be assessed after the results of the initial troponin are available in some cases. CTCA, computed tomographic coronary angiography; ED, emergency department; CAD, coronary artery disease; ECG, electrocardiogram.

#### Eligibility criteria

Eligible clinicians will include ED physicians and mid-level providers caring for patients with chest pain. Eligible patients will include adults (>17 years of age) presenting to the ED with a chief complaint of chest pain who are being considered by the treating clinician for admission for additional observation and cardiac stress testing or for further cardiac testing with coronary CT angiography. Exclusion criteria are listed in Figure 
1. Data will be collected on all patients assessed for eligibility, including the number of excluded patients, the rationale for each exclusion, and the number of patients who decline consent to participate in the study in accordance with the CONSORT guidelines for reporting randomized trials
[18].

#### Integrating patient recruitment, consent, and delivery of the intervention in the flow of patient care

Figure 
1 shows how the process of patient recruitment, consent, randomization, and delivery of the intervention will integrate with the flow of patient care. We will attempt to assess patient eligibility and obtain consent shortly after the clinician has evaluated the patient and interpreted the initial ECG, but before the result of the first cardiac troponin is available. Patients who are otherwise eligible for the study but in whom the first cardiac troponin result is greater than the 99th percentile reference limit will be excluded prior to randomization. Once the initial cardiac troponin result is determined to be negative, the patient will subsequently be randomized using a centralized web-based mechanism to either the decision aid or usual care arm. Patients who are randomized to the decision aid arm will then discuss with their clinician their 45-day risk for an adverse cardiac event and engage in shared decision-making. Patients randomized to usual care will receive no intervention. The number and timing of subsequent cardiac troponin measurements will not be prescribed by the study protocol. Instead patients will subsequently undergo serial cardiac troponin measurements to rule out AMI according to the institutional protocol at each participating site.

#### Patient and stakeholder engagement in the trial

Patients, their caregivers, and other key stakeholders were and will be engaged throughout the entire research process and will comprise the patient and stakeholder advisory group.

The emergency department Patient Advisory Council, which consists of five individuals who have contributed the patient’s perspective to several practice and quality improvement initiatives at Mayo Clinic Rochester - an ED quality specialist, three patients, and a nurse representative - provided feedback on the grant proposal and will continue to inform on the conduct of the trial and the interpretation of the results when the trial is complete. A patient and caregiver representative were engaged in the preparatory phases of research and assisted in the development and iterative refinement of the CPC decision aid, provided feedback on the grant proposal submitted for funding, selected the primary outcome for study, are active members on the investigative steering committee, and participate in the study as co-investigators. We will also engage the patient and caregiver representatives in the interpretation and dissemination of the study findings once the trial is complete.

#### Randomization

Patients will be randomized after informed consent is obtained and it is confirmed that all inclusion and no exclusion criteria are met, prior to the patient-clinician discussion of treatment options and patient risk. Allocation will be concealed by means of an online password-protected randomization algorithm designed using Medidata Balance™ Medidata Solutions, New York City, USA. Patients will be dynamically stratified
[19] by enrolling by site, age and sex because of the known association of age and sex with cardiovascular risk and the availability of these data at the time of enrollment. Allocation will be based on a 1:1 ratio between the intervention and usual care arms. Though we will not be able to blind patients and clinicians to use of the decision aid, we will blind the investigators and individuals not involved in providing care to the patient allocation.

### Intervention arm

#### Refinement of the decision aid

The initial CPC decision aid was developed and tested in a single-center pilot randomized trial at the Mayo Clinic in Rochester, Minnesota, United States, as described previously
[11]. The process of decision aid development was evidence-based, iterative, involved patients and key stakeholders, was based on participatory action research, used design approaches to ensure the final iteration met the needs of end-users, and resulted in a tool that satisfied International Patient Decision Aid Standards (IPDAS)
[20]. After the pilot trial was completed and prior to beginning the multicenter trial, the decision aid underwent additional revisions based on input from the patient [name] and caregiver [name] representatives engaged in the trial and the investigative team in order to increase the clarity of the decision aid and improve patient comprehension. The refined CPC one-page decision aid is included in Figure 
2.

**Figure 2 F2:**
[figure not shown]
**The Decision Aid.** The decision aid describes for patients the rationale for, and results of, the initial emergency department evaluation (electrocardiogram, initial cardiac troponin level) and the potential utility of additional cardiac testing. A reliable estimate of the risk of an acute coronary syndrome within 45 days, obtained from a quantitative pretest probability (QPTP) web-tool developed and tested by Kline *et al*. [5,15,16], is included. The decision aid will be individualized to the patient based on the results of the QPTP risk calculator. The risk estimate is displayed using a state-of-the-art risk communication pictograph using an ordered icon array displaying natural frequencies, and a prose description of patient risk (for example, out of every 100 patients with factors like yours, 1 had a heart attack or pre-heart attack diagnosis within 45 days, 99 did not) to account for differences in numeracy preferences between patients. The decision aid also provides explicit management options (admission with urgent cardiac stress testing, follow-up with a cardiologist or the patient’s own primary care physician within 24 to 72 hours, or have the clinician make the decision on the patient’s behalf) for the clinician and patient to consider when reaching a shared decision.

In the process of preparing for the trial it became clear that one of the participating sites (University of Pennsylvania) frequently used coronary CT angiography in chest pain patients at low-risk for ACS in lieu of cardiac stress testing. To ensure the decision aid facilitated a conversation that included options relevant to the setting in which patients are frequently considered for coronary CT angiography, a second version of the decision aid was developed for use at this site (Figure 
3).

**Figure 3 F3:**
[figure not shown]
**Decision aid that includes the option of coronary CT angiography.** This version of the decision aid was developed for use at the University of Pennsylvania emergency department (Pennsylvania, United States) in which coronary CT angiography is frequently used in lieu of cardiac stress testing.

Participating clinicians were trained by means of a one-hour grand rounds presentation given by the lead investigator at each participating site, as well as a training video that demonstrated use of the decision aid in a simulated patient encounter. The lead study coordinator at the central coordinating site trained each of the study coordinators at the participating sites to ensure comprehension of the study protocol and the standardized execution of study procedures. As was done in our pilot trial, study coordinators will offer to provide the treating clinician a concise refresher of the content included in the decision aid at the time of patient enrollment. Videos of the patient-clinician disposition discussion will be obtained to assess the fidelity of the use of the decision aid in the intervention group and to monitor for contamination in the control group. Video and audio recordings will be consented to separately and are not required for participation in the trial.

#### Delivery of the intervention

For patients randomized to the decision aid arm, the study coordinator will collect each of the variables entered into the quantitative pretest probability (QPTP) PREtest consult Inc. Charlotte, USA calculator, ask the treating clinician to verify and sign off on their accuracy, generate the 45-day estimate of ACS risk, and select the decision aid corresponding to the appropriate level of risk. The study coordinator will then provide the clinician with a color copy of the decision aid prior to the disposition discussion with the patient and offer to provide a concise refresher of the content included in the decision aid. The treating clinician will then, using the decision aid as a tool to facilitate discussion, educate the patient regarding the rationale for their evaluation up to that point in the ED visit, communicate the 45-day risk for a heart attack or pre-heart attack, and engage the patient in a shared decision regarding whether to obtain further cardiac testing after AMI has been ruled out by cardiac troponin testing, to follow up as an outpatient within 72 hours of the ED visit with a cardiologist or their primary care physician, or to have the emergency clinician decide on the patient’s behalf.

#### Usual care

For patients randomized to the usual care arm the clinician will discuss the results of diagnostic investigations and management options with the patient in that clinician’s usual fashion. The patient’s risk will be calculated using the QPTP calculator for study purposes, however, the patient and clinician will be blinded to the QPTP-structured risk assessment and the corresponding decision aid in this arm. As in the intervention arm, the clinician-patient disposition discussion will be video and audio recorded to assess the degree to which the clinician engages the patient in the decision-making process and to monitor for contamination in the control arm.

#### Outcome measures

When selecting outcome measures we obtained input from a patient and caregiver representative, clinicians (emergency medicine clinicians and cardiologists), researchers (health services researchers and shared decision-making experts), and a payer representative (Chief Medical Officer of Mayo Clinic Health Solutions). In face-to-face meetings with the patient and caregiver representative it became clear that knowledge was the outcome that was of greatest interest to the patient, so patient knowledge was selected as the primary outcome. Thus, as we did in our pilot trial, we will assess patient’s knowledge regarding their short-term risk for ACS, the potential implications of cardiac testing, the available management options, and the potential risk of radiation exposure through a post-visit survey administered immediately after the clinical encounter
[11].

We will also assess a number of secondary outcomes, including patient engagement in the decision-making process, as measured by the OPTION (observing patient involvement) scale
[21]; the degree of conflict patients experience related to feeling uninformed, as measured by the Decisional Conflict Scale (DCS)
[22]; trust in the physician measured via the Trust in Physician Scale (TPS)
[23]; patient satisfaction with the decision made, via a Likert scale on the post-visit survey; and safety as determined by the prevalence of Major Adverse Cardiac Events (MACE) within 30 days of the ED visit.

Consistent with recommendations in a recently published consensus document on ACS research in emergency departments
[24], we will define MACE as AMI
[25], death due to a cardiac or unknown cause, emergency revascularization, ventricular arrhythmia, or cardiogenic shock. We will exclude MACE that occurs during the index admission to the ED but rather focus on events occurring after discharge, in the outpatient setting, which could have potentially been avoided or diagnosed in the ED or hospital. This approach avoids having to adjudicate whether MACE occurring in the ED or hospital were ‘missed’ based on a post-hoc review of potentially incomplete medical records. We will collect data on all MACE that occur up to 45 days from the index ED visit as this is the follow-up interval assessed by the QPTP instrument
[5,15,16]. However, we will compare rates only for events that occur prior to or at 30 days in order to comply with standardized reporting guidelines for risk stratification of ED patients with possible ACS and to facilitate comparison with other ACS risk stratification studies in the extant literature
[26]. A subsequent analysis for all 45 days is planned, with these data to be included as part of an Additional file.

To account for differences in troponin assays between institutions, and for the potential of changing from one assay to another in a given institution during the trial, we will track the specific cardiac troponin assay used at each institution along with that assay’s characteristics (lower limit of detection, 99th percentile reference limit, and 10% coefficient of variation), the absolute value of each troponin measurement, the upper limit of normal used at that institution, and classify whether that value is above the upper limit of normal in each enrolled patient (Additional file
1). Three investigators blinded to the study arm will adjudicate all potential MACE cases and discordances will be noted and resolved by consensus.

One of the goals of this study is to measure the effect of CPC on healthcare utilization. Healthcare utilization will be assessed by measuring the proportion of patients admitted for cardiac testing, the most immediate clinical decision and the greatest driver of utilization, and the patients’ healthcare utilization for the subsequent 30 days after the ED encounter. This will include measures such as hospitalization, re-hospitalization, primary, specialty, and ED visits, and diagnostic and laboratory testing.

#### Data collection

Data documenting the process of screening for potentially eligible participants, application of the eligibility criteria (including the reason for each exclusion), the variables entered into the pretest probability calculator, the arm to which each patient is randomized, and other information best collected in real time will be recorded by study coordinators using a standardized case report form (Additional file
2). Patients’ preferences for understanding numerical information and their preferred approach to participation in medical decision-making will be assessed by a survey administered prior to the clinical encounter (Additional file
3).

Immediate post-visit surveys will collect data on patient knowledge, decisional conflict, patients’ trust in their physician, and patient satisfaction with the decision made (Additional file
4). The degree to which clinicians engage patients in the decision-making process will be assessed by having two trained team members independently review videos of the clinician-patient disposition discussion and apply the OPTION scale
[21].

The patient will be contacted 45 days after enrollment via telephone (primary method of contact) for assessment of safety. If the primary method of contact is not successful the study coordinator will subsequently contact the patient utilizing a secondary method of contact specified by the patient at the time of consent (such as email, a secondary phone number, or mail) for a follow-up assessment. Safety will be assessed using a standardized phone follow-up script to determine whether a MACE occurred and, if so, the date of the event (Additional file
5). Events occurring within 45 days will be recorded to ensure consistency with the duration of follow-up used in the development of the QPTP instrument
[15] and MACE within 30 days will be reported in accordance with standardized reporting guidelines for risk stratification studies of ED patients with potential ACS
[26].

Utilization data will be collected from the electronic medical record at each site, patient self-report, and UB-92 and UB-04 summary hospital billing statements. Whether the patient was admitted to the observation unit or hospital and/or underwent advanced cardiac testing such as cardiac stress testing, coronary CT angiography, or percutaneous coronary angiography, will be assessed by review of the electronic medical record at each institution. Patients will be given a healthcare utilization diary at the time of ED discharge (Additional file
6) and educated regarding its use to facilitate the standardized collection of healthcare utilization data not included in hospital billing statements. Any entries in the healthcare diary, including the date and location of service, will be ascertained at the time of 45-day follow-up. Healthcare utilization within 30 days of the ED visit will be reported for study purposes.

Clinicians will be surveyed immediately after each encounter to determine their perception of the degree of patient involvement in the decision, the helpfulness of the information provided to the patient, and other characteristics of the decision-making process (Additional file
7).

Study data will be collected and managed using REDCap (Research Electronic Data Capture) tools hosted at the Mayo Clinic
[27]. REDCap is a secure, web-based application designed to support data capture for research studies, providing: 1) an intuitive interface for validated data entry; 2) audit trails for tracking data manipulation and export procedures; and 3) automated export procedures for seamless data downloads to common statistical packages.

An independent data and safety monitoring board (DSMB) will monitor safety, scientific, and ethical aspects of the study. The DSMB met prior to beginning enrollment and will meet every six months throughout the duration of the study. Though every effort will be made to minimize post-randomization exclusions, patients will be excluded after randomization if they are found to meet exclusion criteria that were not recognized at the time of enrollment or they choose to withdraw
[28]. Any potential MACE following discharge from the ED or hospital will be reported to the principal investigator and the DSMB. The authority to stop the study will be retained by the DSMB and must be based on consensus.

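### Patients who withdraw are to be excluded after randomisation in an unblinded trial; the rule should be replaced by analysis of all randomised patients as assigned

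*Protocol article*

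**What the plan says.** The rule stands in the paragraph on the data and safety monitoring board (DSMB) under Data collection. It begins "patients will be excluded after randomization if they are found to meet" and continues "exclusion criteria that were not recognized at the time of enrollment or they choose to withdraw", so withdrawal is a second ground beside ineligibility. Its only qualifier is the opening clause, "Though every effort will be made to minimize post-randomization exclusions".

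The Randomization section concedes that "we will not be able to blind patients and clinicians to use of the decision aid". It places randomisation after consent and confirmed eligibility, and "prior to the patient-clinician discussion of treatment options and patient risk". Investigators and others not involved in care are to be blinded.

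The knowledge survey, which is the primary outcome, is given immediately after the encounter (Outcome measures, Data collection). Admission is taken from the medical record. MACE status is ascertained at a 45-day contact, potential cases are adjudicated by three investigators blind to arm, and potential events after discharge go to the principal investigator and the DSMB.

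Statistical considerations allows 5% for loss to follow-up and makes no separate allowance for exclusions.

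**The concern.** A randomised comparison is protected by keeping each patient in the arm assigned. Withdrawal is something a patient does after assignment, here knowing the arm and possibly after the discussion that the intervention is meant to change. If withdrawal differs between arms in rate or in kind, removing those patients leaves groups that randomisation did not form. The rule also treats withdrawal as a ground for exclusion rather than as a point after which data may be missing. A patient who withdraws during the 45 days may already have supplied the primary outcome and the disposition.

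The second ground is less troubling. A criterion that was met but not noticed at enrolment is a fact from before randomisation, and removing such patients by the same blinded process in both arms need not bias the result. The weakness is that the text does not say the discovery or judgement is made blind to arm, and the treating clinicians know it.

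At stake are the estimates for knowledge and admission, and the MACE estimate, where events are expected to be so few that each one matters to the reported difference.

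**Working it through.** **Inputs from Statistical considerations and Table 1.** 930 enrolled; 5% loss; 884 with complete data; knowledge 44% (SD 23.3) against 60% (SD 20.9); admission 77% against 67%; MACE 0% in both arms, one-sided alpha 0.05, margin 5 points. From Randomization: "Allocation will be based on a 1:1 ratio between the intervention and usual care arms", so 465 per arm enrolled and 442 per arm with complete data.

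**The plan's own figure.** 930 × (1 − 0.05) = 883.5, which rounds to 884. It reproduces, and the whole allowance is used by loss to follow-up.

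**Assumptions.** The article gives no expected exclusion rate. I take 2% and 5%, and the extreme case in which exclusions fall in one arm only.

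**Admission.** If a fraction f of the decision-aid arm is excluded and a share e of those were admitted, the remaining rate is (0.67 − f·e)/(1 − f).
- f = 5%, all admitted: (0.67 − 0.05)/0.95 = 65.3%, a shift of −1.7 points.
- f = 5%, none admitted: 0.67/0.95 = 70.5%, a shift of +3.5 points.
- f = 2%: the same two extremes give −0.7 and +1.4 points.

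The planned difference is 10 points.

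**Knowledge.** If the 5% excluded from the decision-aid arm score one SD (20.9 points) below that arm's full mean, the remaining mean rises by 0.05 × 20.9/0.95 = 1.1 points, against a planned 16.

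**MACE, chance of losing an event.** Assume a true rate between 0.2% and 2%, that is 930 × 0.002 = 1.9 to 930 × 0.02 = 18.6 events, and exclusion unrelated to outcome. The chance that at least one event is lost is 1 − (1 − f)^events:

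| Excluded | 1.9 events | 18.6 events |
|---|---|---|
| 2% | 4% | 31% |
| 5% | 9% | 61% |

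**MACE, effect on estimate and verdict.** Newcombe two-sided 90% intervals, whose upper limit matches a one-sided 0.05 test. Counts are assumed (decision aid against usual care).

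| Counts | Per arm | Difference (points) | 90% interval |
|---|---|---|---|
| 5 v 0 | 465 | 1.08 | 0.28 to 2.19 |
| Those 5 patients excluded: 0 v 0 | 460, 465 | 0 | −0.58 to 0.58 |
| 9 v 0 | 442 | 2.04 | 0.99 to 3.47 |
| 14 v 0 | 442 | 3.17 | 1.90 to 4.85 |
| 15 v 0 | 442 | 3.39 | 2.09 to 5.12 |

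A 1% MACE rate in 884 patients gives 884 × 0.01 = 8.8, or about 9 events. Even with all nine in the decision-aid arm, the upper limit of 3.47 is below 5, so non-inferiority is met whether or not those patients are kept. The margin is first missed at 15 against 0 with 442 per arm, or at 16 against 0 with 465 per arm (15 gives 4.87, 16 gives 5.12). Within 0 to 9 events, exclusion changes the estimate and interval and leaves the verdict as it was.

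**The case against.** The case on the other side has five parts.

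- **The article is condensed.** Analysis populations and the handling of data after withdrawal are commonly left to the full protocol or analysis plan, so the absence of an intention-to-treat statement is no finding. That stands, and this point does not rest on it. It rests on an exclusion rule that the article does state.
- **The rule does not say that data are discarded.** It sits under Data collection, and exclusion could mean only an end to study procedures. It is true that discarding is not stated. But the sentence speaks of post-randomisation exclusions and puts withdrawal beside ineligibility, so removal from the comparison is the more natural reading. If the sponsor means something else, one sentence would settle it.
- **Late-found ineligibility concerns baseline facts.** This stands. A reader might infer that patients could be dropped for anything that comes to light after randomisation; the wording about criteria not recognised at enrolment does not support that. What is left is the unstated blinding of the judgement.
- **Safety events are protected.** Adjudication is blind to arm and potential MACE go to the DSMB, so events are not lost to oversight. Neither safeguard says that an excluded patient's event stays in the comparison between arms.
- **The sizes are small and the examples are extreme.** This largely stands. One-sided exclusion of patients who all have the same outcome is a bound, and the pilot lost only 2% to follow-up.

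**Conclusion.** The concern holds for withdrawal and, more weakly, for late-found ineligibility. The article fixes a rule that, on its natural reading, lets conduct after randomisation, by patients who know their arm, decide who is compared.

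The expected effect is small for knowledge (about 1 point in 16) and at most a few points for admission (−1.7 to +3.5 against 10). Both figures assume 5% excluded from one arm only, with the outcome patterns stated above. For MACE the estimate and interval can change visibly: an assumed 5 against 0 becomes 0 against 0, which bears on the article's hypothesis of no increase in adverse events.

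A reader might go further and infer that dropping a handful of patients could decide the non-inferiority result. The plan's own margin does not support that: at 0 to 9 events the verdict is the same with or without them. Severity is moderate.

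**What to change.** Replace the rule with a statement that all randomised patients are analysed in their assigned arm, using all data collected up to withdrawal and, where consent allows, medical-record data afterwards, including for MACE.

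Permit exclusion for ineligibility only on facts that existed before randomisation, judged by people blind to arm and outcome. Report the number and reasons by arm, and add a sensitivity analysis that restores those patients.

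The cost is a change of wording and one additional analysis. Its downside is that a few ineligible patients would slightly dilute the effect in the sensitivity analysis.
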